### Intervention

The proposed optimised behavioural intervention consists of up to six sessions (one group session in which couples are initially together and subsequently split into single-gender subgroups, a second single-gender group session, and four couples’ counselling sessions). The intervention is hypothesised to provide information and education around HIV testing and treatment, transform couples’ motivation for looking after their health as a couple rather than as individuals, as well as to improve communication, intimacy and trust necessary for mutual decision-making about behaviours related to sexual risk behaviour and testing for HIV.

Couples will not be reimbursed for the intervention sessions as these are perceived to offer a benefit to couples in and of themselves, and this offers a more feasible set-up to scale-up and implement more widely. This is different to the Uthando Lwethu study which offered reimbursement of ZAR50 (approximately GBP 3.00, as of January 2014) per person per session for all intervention sessions.

#### Group session 1

This first group session will be comprised of a half-day workshop focusing on general health issues in couples, including health conditions assessed at the general couples health screening (blood pressure, diabetes, curable STIs, obesity and HIV). Both partners participate together in the first section of the workshop, with approximately 15–20 couples in each group. Subsequently, the couples will be split into male-only and female-only sub-groups to begin discussing sexual health, family planning, HIV awareness, and benefits and barriers to testing. Community members living with HIV and others who have recently tested HIV negative, and have previously spoken publicly about their HIV testing history and HIV status, will be invited to attend and facilitate a dialogue around couples testing and impact on relationships during the single-gender session.

#### Group session 2

Approximately 1 week after completion of the first half-day workshop, couples will receive a second half-day workshop on couples dynamics, communication skills, and reproductive health issues (e.g., sexual health, HIV). The second workshop will be organised as separate parallel men- and women-only group sessions to facilitate discussion. The groups will be run by a gender-matched facilitator. In the single-sex group session, participants will undertake exercises on topics including couples’ dynamics, such as power, trust, commitment, gender norms and communication skills training. Refreshments will be provided for study participants.

#### Couples Counselling sessions

Couples will receive up to four couples’ counselling sessions, each lasting 1 to 2 h. These sessions will be led by a trained counsellor. The sessions include communication skills training, problem-solving, setting health-related relationship goals, and exploring perceived benefits and barriers to HIV testing within the couple. Each session will be spaced approximately 1 week apart at times convenient for couples.

If the couple engages in couples HIV testing at an earlier point in the intervention, the counselling structure will change, such that if a couple tests together after 1–2 counselling sessions, they will be offered one final counselling session, which would include the content of counselling session 4 in terms of planning for their future together.

If a couple misses a session, staff will call each partner to reschedule the appointment. If the couple cannot be reached, and they have consented to being visited at their home, a staff member will go to their home to follow up. If a couple has not completed the intervention sessions within 3-months of group session 1, no further intervention sessions will be arranged for this couple. Based on our experience in the Uthando Lwethu study, if a couple is motivated to take part in the intervention, all sessions will be completed within this 3-month window.

##### Couples session one

In the first couples counselling session, couples will re-visit and practice the communication technique introduced in the second group session and describe to each other what happened in their single-gender sessions. Couples will explore the basic expectations they have in their relationship related to their health and set health-related relationship goals and plans for how they will meet these. In addition, couples will engage in exercises to learn and practice helpful problem-solving strategies. The couples will also engage in a commitment exercise to remind them of their partner’s and their relationship’s positive aspects.

##### Couples session two

Couples will begin the second couples counselling session with a brief check-in about their time since the last session and ask about progress in their health-related relationship goal. The counsellor will also help the couple review the first counselling session.

The counsellor will help the couple discuss the barriers or facilitators they face in meeting their expectations around HIV, risk, and couples testing. Couples will identify a barrier they would like to address during the session. The couples will then use the communication technique to engage in problem-solving exercises to talk about the ir identified barrier.

##### Couples session three

In the third couples counselling session, the counsellor will check in with couples about their time since the last session and ask about progress in their health-related relationship goal. When the couple has finished this review, if appropriate, they will be asked to name two other barriers they face in meeting each other’s expectations related to HIV. For the remainder of the session, the couples will use the communication technique to engage in problem-solving exercises to address their identified barriers.

##### Couples session four

The fourth and final couples counselling session will begin with a brief check-in with the couple about their time since the previous counselling session, ask about progress in their health-related relationship goal and their thoughts on what they have learned over the course of the intervention.

The counsellor will facilitate a discussion about the couple’s plan to move forward and use the skills they learned in their counselling sessions.

The couple will also discuss upcoming issues and events that may present a challenge for them and how they can remember to use the skills they gained during the intervention. Specifically, the counsellor will ask the couple to talk through the skills they have learned and resources they identified such as support from family or community members.

Finally, the counsellor will wrap up the session by summarising the specific issues that the couple worked on during the counselling sessions and the tools they used to address them. The counsellor will help the couple set goals for the future in light of the new tools and resources they gained and identified.

### Study procedures and follow-up

#### Baseline survey

The baseline survey includes measures of domestic violence and mutual disclosure to confirm the couple’s eligibility. In addition, the survey includes measures of relationship domains such as satisfaction, communication and measures about HIV and reproductive health (e.g., fertility intentions, HIV knowledge and risk perception, and sexual behaviour). All measures were previously used in Uthando Lwethu. We have dropped some demographic questions from the Uthando Lwethu baseline questionnaire, which were deemed unnecessary, and added questions on self-reported health status (e.g. raised blood pressure and diabetes) and health behaviours, as recommended by the WHO STEPs protocol [34].

#### Enrolment in the intervention

Couples will arrive together at the venue for the first group session. In the Uthando Lwethu study approximately two-thirds of couples who remained eligible after the baseline survey joined a group 1 session. Thus, our target of enrolling 180 couples refers to the number of couples attending group session 1.

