Between 2012 and 2015, the Uthando Lwethu Study tested the efficacy of an interdependence theory-based behavioural couples-focused intervention to increase participation in CHTC in South Africa among couples who had never tested for HIV together or mutually disclosed their HIV status [8]. Three hundred thirty-two couples were randomised to the intervention arm (168 couples) or the control arm (164 couples). The intervention arm received two group sessions and four couples counselling sessions, focused on problem-solving and communication skills and was highly effective in increasing the proportion of couples that decided to test for HIV together within 9 months after enrolment, (42% v. 12% [*p* < 0.001]) compared to the control group [9]. Concerned that, in a high HIV prevalence and continued HIV incidence setting [10], 58% of intervention couples did not choose to test together during the Uthando Lwethu study, we optimised the Uthando Lwethu intervention using the Person-Based Approach to intervention development and optimisation [11]. The details of the process of optimising the intervention have been published elsewhere [12]. In brief, a qualitative study was conducted with 20 purposively sampled couples who were formerly enrolled in the intervention arm of the Uthando Lwethu Study, and with 5 study staff who delivered intervention components, with the aim of exploring experiences of the intervention and barriers to testing. The past participants sampled included couples who did not attend couples counselling sessions and did not test for HIV together, some couples who attended all couples counselling sessions and tested for HIV together during follow-up, and others who only took up part of the intervention, with or without deciding to test for HIV together. Developing guiding principles and a logic model that showed how the optimised intervention would increase uptake to CHTC ensured that optimisations were grounded in the local context and drew on theoretical constructs [12]. The optimised intervention still involves two group sessions and up to four couples’ counselling sessions but differs from the Uthando Lwethu intervention in session content, involving community members speaking publicly about their HIV testing history and HIV status, and the possibility that the number of counselling sessions provided will be less if the couple engages in couples HIV testing at an earlier point in the intervention.

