In South Africa, rates of intimate partner violence (IPV) reported in the literature are high [13]. The most recent Demographic Health Survey in South Africa (2016) reports one in four (26%) ever-partnered women age 18 or older have experienced physical, sexual, or emotional violence committed by a partner in their lifetime [14]. In the Uthando Lwethu study, among the 448 couples screened for eligibility, there were almost no reports of a history of IPV, and no reports of IPV during study follow-up were recorded. The Uthando Lwethu study excluded couples with a recent history of IPV (within last 6 months) because it was recognised that such couples would need both a different intervention and, support by staff with specific training and experience of counselling couples experiencing ongoing IPV. However, the Uthando Lwethu study included participants where an experience of IPV had occurred less recently. Thus, minimising selective exclusion of people at a high risk of HIV-infection.

To normalise HIV testing in research studies, in recent years HIV testing is increasingly offered as part of a broader health check [15–17], which led us to include screening for other conditions as part of our CHTC offer during follow-up, and to promote this as an opportunity for ‘couples health screening’.

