### Outcomes

#### Primary outcome

The primary outcome measure is the proportion of couples that take up couples HIV testing as part of a health screening visit during study follow-up i.e. within 4 months from the date of the first group session, compared to the equivalent proportion in the intervention arm of the Uthando Lwethu study (historical controls).

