### Statistical considerations

#### Sample size, accrual, follow-up

In the Uthando Lwethu study, 39% of the intervention arm (65/168 couples) had taken up testing together for HIV by 4-months follow-up. A sample size of 180 couples in the Igugu Lethu study provides more than 85% power, at the 5% level, to detect a 40% increase in the proportion testing together, i.e. change from 39 to 55% between the two versions of the intervention, and allow for 5% lost to follow-up or break-up by 4-months.

We aim to accrue the sample of couples over approximately 16 months of active recruitment. Given the continued SARS-CoV-2 pandemic, changes in public health and research-related restrictions may mean a slower rate of recruitment. We will recruit in waves and aim to have approximately 20 couples participate in a round of intervention activities, and will continue to conduct intervention rounds until we achieve our goal of 180 couples. We will follow the couples for a total of 4-months from the date of the first group session in each intervention round.

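### The primary comparison is not shown to be like with like: Igugu Lethu counts couples from attendance at group session 1, while the benchmark is 65 of the 168 couples randomised in Uthando Lwethu

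*Protocol article*

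**What the plan says.** **Igugu Lethu denominator and clock.** Under Enrolment in the intervention, the article notes that in Uthando Lwethu "approximately two-thirds of couples who remained eligible after the baseline survey joined a group 1 session" and concludes that "our target of enrolling 180 couples refers to the number of couples attending group session 1". The Primary outcome section counts uptake "within 4 months from the date of the first group session".

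**Benchmark.** Under Sample size, accrual, follow-up: "39% of the intervention arm (65/168 couples) had taken up testing together for HIV by 4-months follow-up". The Background identifies 168 as the size of the randomised arm: "Three hundred thirty-two couples were randomised to the intervention arm (168 couples) or the control arm (164 couples"). It describes the earlier trial's 9-month result as counted from enrolment, and does not place randomisation before or after group session 1.

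**Analysis.** Data analysis specifies an unadjusted chi-square test of the two proportions, with logistic regression only if baseline characteristics differ substantially.

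**Qualifying test.** The Primary outcome section counts couples testing that forms part of the health screening visit. Data analysis speaks only of couples who test for HIV. The section on the couples health screening visit anticipates that some couples will test together at another venue.

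**Payment.** Uthando Lwethu paid ZAR50 per person per intervention session. Igugu Lethu pays nothing for sessions (Intervention section).

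**The concern.** Attendance at group session 1 is a filter. By the article's own account, about a third of Uthando Lwethu couples who were eligible after baseline never passed it. Couples who do pass it are presumably more likely to go on to test together. If Igugu Lethu applies the filter before counting and the historical arm does not, uptake will look higher in Igugu Lethu even when the optimised intervention is no better.

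The planned adjustment cannot repair this. Logistic regression on baseline covariates does not change who is in the denominator or when the clock starts. The article's reflection on historical controls, in the section on the COVID-19 pandemic, concerns the pandemic only.

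This single comparison with historical controls carries the whole efficacy claim, so an unexplained difference in denominators goes straight into the primary estimate. The two wordings of the qualifying test add a smaller ambiguity: a couple who tested together elsewhere would count under one section and not under the other.

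**Working it through.** **1. The plan's own power figure.** Inputs from the sample-size section: 65/168 or its rounded 39%, a target of 55%, and 180 couples (171 after the 5% allowance). Two-sided 5% is assumed, since sidedness is not stated. With pooled variance under the null,

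power = Φ((|p2 − p1| − 1.96·SE0) / SE1).

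- 65/168 = 38.7% against 55%: 86.5% with 180 couples, 85.6% with 171.
- 39% against 55%: 85.1% with 180, 84.2% with 171.

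The claim of more than 85% is reproduced to within a point, with 168 as the comparator size. The sample size is not the problem; the meaning of the 168 is.

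**2. Could all randomised couples have been group session 1 attenders?** Inputs: 332 randomised and "among the 448 couples screened for eligibility" (Background), and about two-thirds joining group session 1 (Enrolment in the intervention).

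- Attenders if every screened couple had been eligible: 2/3 × 448 = 299, fewer than 332.
- Eligible couples needed to yield 332 attenders: 332 ÷ (2/3) = 498, more than 448.
- Attendance rate needed even if all 448 had been eligible: 332/448 = 74%.

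The three figures do not fit an attenders-only 168 unless two-thirds is a loose rounding of at least 74%, or 448 refers to some narrower screening stage.

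**3. Benchmark on the Igugu Lethu definition.** Let a be the share of the 168 who attended group session 1. The documents do not give a. Assuming all 65 testers attended, the rate among attenders is 65/(168·a). The last column is the probability of a significant chi-square if Igugu Lethu's 180 couples have exactly that rate (no better intervention) and are compared with 168 couples whose rate is 65/168, using the step 1 formula.

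| a (assumed) | Attenders | Benchmark | Chance of a significant result with no better intervention |
|---|---|---|---|
| 100% | 168 | 38.7% | nominal |
| 90% | 151 | 43.0% | about 13% |
| 85% | 143 | 45.5% | about 25% |
| 80% | 134 | 48.4% | about 44% |
| two-thirds | 112 | 58.0% | about 95% |

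The 55% target would be met with no better intervention once a falls to 0.387/0.55 = 70%.

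**4. Effect on a result that hits the target.** 99/180 = 55%. Chi-square without continuity correction: against 65/168, p = 0.002; against 65/143 (a = 85%), p = 0.088. Nothing in the documents selects 85%; it shows how quickly the conclusion can change.

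**The case against.** The strongest reply is that the 168 may already be attenders. The article says that about two-thirds of all eligible Uthando Lwethu couples joined a group 1 session. If only the intervention arm had been offered it, no more than 168/332 = 51% of randomised couples could have joined. That fits a group session 1 held before, or regardless of, allocation, and the 180-couple rule then simply copies the earlier trial's entry point. The Primary outcome section also calls the historical figure the equivalent proportion, and the timing of randomisation belongs to sources not shown here. This stands as a reason not to call the mismatch proven. It does not settle the matter: on that reading 332 attenders still have to come from 448 screened couples at about two-thirds, and the arithmetic does not close.

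On the clock alone, little is at stake. Uthando Lwethu uptake was 39% at 4 months and 42% at 9 months, about 3 points in 5 months. At that later pace, a shift of a few weeks is worth less than one point.

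Three stronger readings are tempting, and the documents do not support them:

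- *Lost couples are removed from the analysis.* The phrase "allow for 5% lost to follow-up or break-up by 4-months" is a sample-size allowance only. No section takes lost or separated couples out of the denominator, a screening-visit test is recorded by the study itself, and the break-up questionnaire asks about testing up to separation. If lost non-testers were excluded, 38.7% would become 0.387 × 180/171 = 40.7%, about 2 points, but that exclusion is not in the plan.
- *Unpaid attendance inflates uptake.* Couples who come without payment may be more motivated, but lack of payment may also reduce attendance at later sessions. The net direction is unknown. The change is openly stated in the article.
- *The two outcome wordings favour Igugu Lethu.* Counting only screening-visit tests could only lower Igugu Lethu uptake. The wording in Data analysis may be shorthand; the point is ambiguity, not a bias in a known direction.

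**Conclusion.** The concern holds in this form: the article does not establish that the two proportions share an entry point, a time zero and a definition of a qualifying test, and its own figures suggest that the 168 include couples who never attended group session 1. A reader might infer that the comparison is biased by a known amount; the documents do not support that. If Uthando Lwethu randomised at or after group session 1, the denominators match on attendance, and only the payment change and the outcome wording remain. If it randomised earlier, the comparison favours Igugu Lethu, by 4.3 points at 90% attendance (43.0 − 38.7), 9.7 at 80% and 19.3 at two-thirds, against a planned difference of 16 points. These sizes rest on assumed attendance and on all 65 testers having attended; testers among non-attenders would make them smaller. The question should be settled before the analysis, because the comparison is the only efficacy evidence and baseline adjustment cannot correct a different denominator.

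**What to change.** 1. From the Uthando Lwethu records, compute the intervention-arm proportion on the Igugu Lethu definition: couples who attended group session 1, 4 months from that date, and the same qualifying tests. State when randomisation took place relative to that session. Use the result in place of 65/168 if it differs, and recheck the power statement against it.
2. State that every enrolled couple stays in the denominator in both studies, with lost or separated couples who have no recorded couples test counted as not tested.
3. In Data analysis, name the outcome exactly as the Primary outcome section defines it, and say how couples tests at another venue are handled.
4. Report the change from paid to unpaid sessions as a limitation of the historical comparison.
5. Only if Uthando Lwethu randomised before group session 1, consider a sensitivity analysis with all baseline-eligible couples as the denominator. Otherwise non-attenders belong to no arm and it cannot be built.

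The cost is a small re-tabulation of data from the earlier trial and a few sentences of analysis text, with no new participants or procedures. The downside is that the benchmark may rise, leaving less room to show an improvement.

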#### Follow- up

All enrolled couples will have follow-up assessments in person or by phone at 4-weeks and at 4-months after the Group 1 session. The follow-up questionnaires used at 4-weeks and 4-months are similar to the follow-up questionnaire used in the Uthando Lwethu study. Each follow-up visit will follow similar procedures as detailed for the baseline survey. Each member of the couple will be interviewed separately, ideally at the same time, by a gender-matched interviewer.

During the baseline consent process, participants will be asked if they are willing to be contacted by phone for appointment reminders, as well as follow ups for missed appointments. They will also be asked if they are willing to be visited at home if they miss a study visit. After participants have consented to participate in the study, they will be asked to fill out a tracking form. This form will collect contact details, to facilitate reminder calls for scheduled appointments, as well as follow up calls for missed appointments. Additionally, if the participant agreed to be visited at home after missing a study visit, they will provide detailed information about the location of their primary residence, as well as any alternative residences. Contact information will be updated during each follow up visit.

At the end of the 4-month interview, participants will receive a certificate of study completion, an end of study information sheet and they will be asked to provide written consent to contact for future studies.

